### Study intervention (group B)

At the randomisation/baseline visit (month 0, see figure 1), the study dietitian will implement the following:*Calculation of fluid prescription*. Participants will be advised to drink a prescribed volume of fluid per day (preferably tap water), based on the free water clearance formula, to reduce their urine osmolality to ≤270 mOsmol/L plus an amount to account for insensible losses (appropriate for climate and daily activity).^30 31^ The calculation is as follows:^17^

$$\begin{array}{l} Prescribed\;fluid\;intake\;(mL)\;\\ \;=\frac{total\;solutes\;(mOsmol)\;(mL)}{270}+insensible\;losses\;(mL) \end{array}$$
Total solutes (urine osmolality×urine vol (mL)) is the mean derived from two 24 hours urine samples collected between the screening visit and the randomisation/baseline visit.*Dietary counselling*. A high dietary solute load (due to high salt and protein intakes) requires a higher fluid intake to maintain urine dilution.^11^ Participants will be educated about the importance of dietary solute intake in determining obligatory urine volume (ie, the minimum urine volume required to excrete the daily solute load).^32^ The study dietitian will take a detailed diet history and provide tailored dietary advice to enable participants to achieve and maintain a moderate protein intake (0.75–1.0 g/kg/day) and limit sodium intake to 80–100 mmol/day.^19^ If the calculated prescription is >3 L/day, the participant will be advised to gradually increase fluid intake until target urine osmolality is reached and focus on reducing dietary solutes to reduce the risk of hyponatraemia.*Review of lifestyle and environmental factors*. The participant’s lifestyle, personal preferences and occupation will be recorded and reviewed when providing individualised techniques for promoting adherence to fluid intake. Participants will be provided with 3×1 L reusable water bottles to help keep track of their fluid intake, and will be encouraged to drink evenly throughout the day and replenish with each episode of nocturia.*Self-monitoring of fluid intake and treatment efficacy*. Aids have been developed to assist participants with self-monitoring, including a paper-based diary or web-based/smartphone compatible tool to self-monitor fluid intake, and urine dipsticks will be provided to record urine-specific gravity (USG). Participants will be shown how to read their USG and will be asked to test it during the late afternoon (16:00–20:00 hours) at least once daily in the first 2 weeks of the study, at least twice weekly for the first 6 months and then at least monthly for the duration of the study. An USG of ≤1.010 indicates a spot urine osmolality of ≤270 mmol/L, meaning that fluid intake in the past few hours has been adequate. Participants will also be briefed on receiving and responding to short message service (SMS) text messages (or emails if they do not own a mobile phone) requesting the results of a late afternoon USG measurement (see below), as well as on the schedule of telephone calls (see below).*Scheduled telephone calls and follow-up study visits*. Participants in the intervention group will be contacted by telephone (at weeks 1, 3 and 6, then monthly in year 1, and 3-monthly for years 2–3) and reviewed face-to-face at all study visits by the Study Dietitian to assess compliance with fluid intake, discuss USG results, ensure that blood and urine samples are collected and to record any AEs and new medications commenced. If necessary, the fluid prescription will be adjusted depending on the results of progress 24 hours urine osmolality and USG. The study dietitian will monitor compliance with protein and sodium recommendations using 24 hours recalls at all study visits.*Response to SMS text messages*. To provide a quantitative measure of adherence, participants in the intervention group will be required to reply (within 12 hours) to an SMS message requesting the results of a late afternoon USG. The SMS message will be delivered randomly twice a week in months 0–6, then monthly for the duration of the study.*Rationale for the intervention*. Previous trials in patients with recurrent nephrolithiasis in Italy and Israel have shown that a long-term increase in fluid intake can be achieved with targeted education provided at clinic visits alone^33 34^ but, for the current study in Australia, telephone coaching by a dietitian and the above tools are included to boost compliance and continued participation.^35^ A systematic review revealed that self-monitoring of USG is a critical tool to enhance the implementation of increased fluid intake in clinical trials.^36^ SMS texting is a method preferred by consumers in health interventions.^37^

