For several years, it has been suggested that the suppression of AVP by increasing fluid intake could also slow renal cyst growth in ADPKD.^7 11^ In support of the hypothesis, preclinical experiments in the *pck* rat model of PKD showed that increased water intake reduced kidney enlargement,^12 13^ and comparison with separate studies imply that the efficacy might be similar (but with physiological differences) to vasopressin receptor antagonists.^14^ However, whether this hypothesis is also true in humans with ADPKD remains unknown. The data available are limited to a single post hoc analytical study,^15^ two short-term interventional trials (<1 week in duration) without control groups,^16 17^ and a single, small, quasi-randomised observational cohort study of 12 months’ duration, which paradoxically suggested that increased fluid intake increases renal cyst growth.^18^ Consequently, evidence-based clinical care guidelines have not included recommendations to increase fluid intake in patients with ADPKD and the matter remains controversial in clinical practice.^19^ Consistent with this view, patients with ADPKD attending a consumer workshop also stated that the role of fluid intake was an ambiguous area that needed urgent prioritisation in clinical research.^20^ An illustrative comment made by a workshop participant was: *‘there needs to be consistency of what doctors say about drinking less or drinking more’*.^20^

Two recent clinical studies reported that prescribed fluid intake could be achieved over a period of 2–4 weeks in patients with ADPKD.^21 22^ In addition, two randomised controlled trials are presently underway to address the role of fluid intake in ADPKD and CKD over a longer duration.^23 24^ However, neither of these studies will specifically address the long-term efficacy of fluid intake on renal cyst growth in ADPKD. Hence, the aim of the current study is to determine the efficacy and safety of prescribed water intake to *prevent* the progression of TKV in CKD (stages 1–3) due to ADPKD (PREVENT-ADPKD) over a 3-year period. The trial commenced study activity in 2015 and as of July 2017 75% of the planned target recruitment has been attained. The current paper provides a summary of the clinical trial protocol.

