### Study visits

*Screening visit (up to month 1.5)*. If a patient meets all inclusion criteria and no exclusion criteria, he or she will be enrolled in the trial. At this visit, participants will have their medical and ADPKD history reviewed, usual fluid intake and kidney pain (using the Halt Progression of Polycystic Kidney Disease (HALT-PKD) study group questionnaire)^29^ assessed. A venous blood sample and spot urine sample will also be collected for DNA analysis and biomarker assessment (see below). Due to the cost and time required to perform genetic testing, the effect of *PKD* mutation type on trial outcomes will be assessed retrospectively. Participants will then be asked to have two 24 hours urine collections and blood tests (for testing baseline electrolytes, eGFR and osmolality) as an outpatient at a local pathology collection centre, and a renal MRI (to assess baseline TKV) will be performed at an external radiology facility. The period from screening to randomisation visits (up to 12 weeks) will serve as the run-in period to confirm the participant’s willingness to adhere to study procedures.*Randomisation and baseline visit (month 0)*. Follow-up medical and ADPKD histories will be taken and venous blood and urine samples will be collected at this visit. Participants randomised to the control group will continue with their usual (ad libitum) water intake and standard treatment. Participants in the intervention group will be advised to adjust their daily water intake for the next 36 months, in addition to continuation of their standard treatment, and be provided with specific instructions, described in the section under *study intervention (group B)*.*Treatment period*. The 3-year treatment period includes repeat outpatient blood and 24 hours urine collections (at 3-monthly intervals in year 1 and 6-monthly in years 2–3), progress MRI scans (at 18 and 36 months) and visits to the study centre every 6 months.*Follow-up study visits (months 6, 12, 18, 24, 30 and 36)*. Progress medical and ADPKD histories and further collections of venous blood and urine will be undertaken at follow-up study visits. Study staff will record answers to specific questions on adverse events (AEs) and kidney pain (using the HALT-PKD questionnaire). In both groups, quality of life will be assessed 6-monthly (month 0, 6, 12, 18, 24, 30 and 36) and usual fluid intake will be assessed annually (month 0, 12, 24 and 36). At the final treatment visit at month 36, intervention group participants will be advised that they may return to their previous ad libitum water intake.*Post-treatment study visit*. This will occur at month 37 for all participants.

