### Measures to reduce bias

The trial intervention is an unblinded behavioural modification. Bias and contamination could be introduced by a participant’s expectations and prior knowledge of the hypothesised role of fluid intake in ADPKD. To minimise the effect of this problem:Both groups will be educated about the fact that fluid requirement in ADPKD is not known and that the intervention may be equally beneficial. The patient information consent form has been written in an objective, neutral manner to accurately reflect current evidence, and does not discuss the hypothesised benefits of fluid intake in ADPKD.Appointments will be scheduled for the two study groups at different times of the day to minimise the chance of control group participants meeting the intervention group in the waiting room.Outcome assessors will be blinded to participants’ treatment allocations.

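### The group B fluid formula ignores usual intake, so a patient with clearly dilute, high-volume baseline urine can be prescribed less than he or she already drinks (minor)

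*Protocol article*

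**What the plan says.** Under Study intervention (group B), the prescription is "based on the free water clearance formula, to reduce their urine osmolality to ≤270 mOsmol/L plus an amount to account for insensible losses". The formula is total solutes divided by 270, plus insensible losses. Total solutes are urine osmolality times urine volume, and the value used "is the mean derived from two 24 hours urine samples collected between the screening visit and the randomisation/baseline visit".

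One rule modifies the calculated value, and it works on the high side: "If the calculated prescription is >3 L/day, the participant will be advised to gradually increase fluid intake until target urine osmolality is reached", with attention to reducing dietary solutes. Later changes are discretionary: "If necessary, the fluid prescription will be adjusted depending on the results of progress 24 hours urine osmolality and USG". Under Study visits, the instruction at randomisation is neutral in direction: "Participants in the intervention group will be advised to adjust their daily water intake for the next 36 months".

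Table 1 requires the 24-hour urine to be completed but sets no limit on its result. Under Secondary end points, one adherence measure is the proportion of the intervention group whose 24-hour osmolality is at or below 270. Systemic AVP activity (serum copeptin, 24-hour urine osmolality and volume) is a separate secondary end point, and the Abstract says that it is compared between the groups.

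**The concern.** The hypothesis in the Introduction is that "the suppression of AVP by increasing fluid intake could also slow renal cyst growth in ADPKD". The formula fixes a urine volume that would bring the baseline solute load to 270. When baseline urine is already more dilute than that, the urine-volume term is smaller than the current urine volume. If the gap is large enough, the prescribed drinking volume is also below current drinking, and a patient who follows it produces more concentrated urine for three years in the arm meant to dilute it.

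The feedback steps all use the same threshold. The article equates a specific gravity of 1.010 or less with a spot osmolality of 270 or less and treats this as adequate intake. The text messages ask for the same reading, and the prescription is revised on osmolality and specific gravity. A patient moved from 150 to about 200 passes each of them and counts as at target in the adherence proportion.

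Such patients are possible at entry. Measures to reduce bias names "prior knowledge of the hypothesised role of fluid intake in ADPKD" as something that could introduce bias and contamination, and recruitment includes the website of a patient foundation.

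**Working it through.** The plan gives no figure on this point to reproduce, so the check is a water balance.

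**Inputs from the protocol article:** the divisor 270; solutes = osmolality U × volume V from the baseline collections; insensible losses added in full; the 3 L/day rule.

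**Assumptions, not in the documents:** water from food and metabolism, W, is 0.5 to 1.0 L/day; the insensible allowance equals the true insensible loss I; solute output is unchanged.

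**Formulas**

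- Usual drinking = V + I − W.
- Prescription = U×V/270 + I.
- Change in drinking = prescription − usual drinking = V×(U/270 − 1) + W. Any gap between the allowance and the true loss adds directly to this.
- Drinking falls only if U < 270×(1 − W/V).
- New urine volume = U×V/270 + W; new osmolality = U×V divided by that volume.

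**Examples**

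| Baseline U, V | Solutes (mOsmol) | Urine term (L) | Minus current V (L) | Change in drinking, W = 0.5 | W = 1.0 |
|---|---|---|---|---|---|
| 150, 3.5 L | 525 | 525/270 = 1.94 | −1.56 | −1.06 L | −0.56 L |
| 200, 3.5 L | 700 | 700/270 = 2.59 | −0.91 | −0.41 L | +0.09 L |
| 250, 3.0 L | 750 | 750/270 = 2.78 | −0.22 | +0.28 L | +0.78 L |

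In the first row the new urine volume is 1.944 + 0.5 = 2.444 L or 1.944 + 1.0 = 2.944 L. Osmolality becomes 525/2.444 = 215 or 525/2.944 = 178, up from 150 but still below 270. The calculated prescription stays at or below 3 L/day for any insensible allowance up to 3 − 1.944 = 1.06 L, so the rule for high prescriptions need not apply.

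**Break-even osmolality, 270×(1 − W/V)**

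- V = 3.0 L: 270×(1 − 0.5/3.0) = 225; 270×(1 − 1.0/3.0) = 180.
- V = 3.5 L: 270×(1 − 0.5/3.5) = 231; 270×(1 − 1.0/3.5) = 193.

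A decrease is therefore secure over the whole assumed range only for clearly dilute, high-volume urine.

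**Adherence proportion (illustrative shares).** Suppose 60% of group B are at 270 or below, and a share p started there and stayed. The proportion of the others who reached target is (0.60 − p)/(1 − p): 60% if p = 0; 0.50/0.90 = 56% if p = 10%; 0.40/0.80 = 50% if p = 20%.

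**The case against.** The strongest reply is that the article condenses a full protocol, and what the dietitian does when the formula falls below usual intake is the kind of detail that document may hold. The stated purpose is to reduce osmolality, and the rationale speaks of increased intake, so a sensible dietitian would probably not tell a high drinker to cut back. This has weight. But the article prints a complete formula and describes its one exception, and that exception is on the high side. Avoiding the low case depends on judgement overriding a stated rule.

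The affected group may also be very small. The article says only that prior knowledge could introduce bias, and elsewhere that the intervention can be difficult to follow on a western diet. That stands: no share is given. The affected patient also remains within the trial's own target, and the advice on salt and protein could lower solutes and offset some of the rise. Both hold, and both limit the harm.

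Three stronger readings are tempting and are not supported:

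- **Every patient below 270 is told to drink less.** The formula adds insensible losses without deducting food and metabolic water, so the patient at 250 and 3.0 L/day is prescribed more than usual under the stated assumptions. At 200 and 3.5 L/day the sign depends on W, and the prescription exceeds 3 L/day once the insensible allowance passes 0.41 L.
- **The trial could not detect the problem.** Osmolality, urine volume and copeptin are compared between groups, 24-hour urine is collected at baseline and follow-up, and usual intake is assessed annually in both arms. The average contrast will be visible, and the number already at target can be counted from the baseline urine.
- **Power is lost.** Without the share of affected patients, no loss can be calculated.

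**Conclusion.** The point holds as a minor one. As printed, the formula takes no account of usual intake, and eligibility does not exclude patients whose urine is already dilute. Below about 270×(1 − W/V), it prescribes less than the patient drinks. In the clearest example, 150 mOsmol/kg at 3.5 L/day, the reduction is 0.56 to 1.06 L/day and osmolality rises to about 178 to 215, which none of the stated checks would flag.

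The size rests on the assumed W, on the insensible allowance matching the true loss, and on unchanged solutes. The proportion of group B at 270 or below is a valid measure of being at target. Read alone, without baseline and control values, it does not separate patients who were moved there from those who started there.

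**What to change.** In the dietitian's procedure, prescribe the larger of recorded usual intake and the calculated volume, unless serum sodium or another safety reason requires less. For group B patients already enrolled, apply this at the next review, since the article allows prescriptions to be adjusted. The floor prevents a decrease; it does not create an increase, and it asks nobody to drink more than at present.

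The cost is about one sentence. Intake is already recorded on the two baseline collection days (Table 2 footnote) and assessed at month 0 in both groups (Study visits). The small downside is reliance on self-recorded intake: under-recording would set the floor somewhat too low.

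As a free addition, tabulate the proportion at 270 or below at baseline and at each follow-up collection in both arms, and show adherence separately for group B patients above 270 at baseline. This uses urine already collected.

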
### Standard treatment

Both study groups will continue to receive the current standard of care for ADPKD as specified by the treating nephrologist. Hypertension will be treated with ACE inhibitors or angiotensin receptor blockers as first-line agents. If hypertension remains inadequately controlled, use of additional antihypertensive agents will be at the discretion of the treating nephrologist, but treatment with diuretics will be contraindicated. The frequency of study visits in the trial is similar to standard nephrological care in ADPKD with CKD stages 1–3.

### Primary end point

The primary end point is the percentage annual change in height-adjusted total kidney volume (ht-TKV) from baseline to 36 months as determined by serial MRI. Dialysis-dependent kidney failure takes decades to develop in ADPKD, making it impractical to use serial changes in serum creatinine and eGFR for assessing treatment efficacy. Ht-TKV is a highly sensitive surrogate marker that measures exponential cyst growth, the key parameter of ADPKD progression and has been used as a primary end point in many pivotal clinical trials. The longitudinal Consortium for Radiologic Imaging Studies of PKD (CRISP-I) study established that the rate of increase in TKV is relatively constant (~5.6 %/year) and can be quantified with high precision by MRI (reliability coefficient, 0.998; mean coefficient of variation, 0.01%).^2^ In CRISP-II, adjusting for height reduced variability in TKV, a baseline ht-TKV value of >600 mL/m predicted development of CKD stage 3 over an 8-year period (area under the curve=0.84; sensitivity, 74%; specificity, 75%).^38^ The magnitude of the rate of increase in ht-TKV predicted the risk of ESKD.

### Secondary end points

*Systemic AVP activity*. Markers will be serum copeptin,^5 24^ 24 hours urine osmolality and volume.*Kidney disease progression*. Markers will be rate of eGFR decline (0 and 3 to 36+ months); resting mean arterial pressure; urine albumin-to-creatinine ratio and kidney pain as assessed by the HALT-PKD questionnaire.*Treatment adherence*. Measured by proportion of the intervention group responding within 12 hours to SMS texts requesting results of the late afternoon USG; proportion of the intervention group with 24 hours urine osmolality ≤270 mOsmol/L.*Safety end points*. Measured by proportion of participants with serum Na^+^ <130 mmol/L; episodes of serious AEs (SAEs).*Patient acceptability*. Measured by a Treatment Acceptability questionnaire^39^ and the proportion of participants withdrawing from the study.*Quality of life*. Measured by the Kidney Disease Quality of Life short form (KDQOL-SF) 1.3 tool.*Healthcare utilisation*. At each study visit, participants are asked if have had any new diagnosis, hospital visits, seen a general practitioner or changed medication since the previous visit.

Study end points were developed to ensure that appropriate health economic analyses can be undertaken at the conclusion of the trial. Future linkage with the Australian and New Zealand Dialysis and Transplant Registry will enable long-term outcomes (eg, time to reach ESKD) to be determined with minimal cost.

### Study measurements

*Ht-TKV*
(Table 2). Renal MRI will be performed three times (at baseline and at months 18 and 36) during the study to assess the annual rate of change in ht-TKV in the study groups. MRIs will be performed in the radiology departments of the respective study centres or an external facility (approved by the investigators). A standardised protocol for image acquisition will be used,^10^ and the MRI protocol and image quality will be validated in test images.^10^ The MRI scans will be de-identified and encrypted, then analysed at the Translational PKD Centre at Mayo Clinic, Rochester, Minnesota, USA by blinded personnel to quantify TKV. Baseline TKV for each patient will be determined by performing kidney segmentation semi-automatically on the T2-weighted MRI using the MIROS software package. This algorithm outputs a complete segmentation after the user quickly defines crude polygon contours of each kidney every third slice.^40^ The interactive toolkit included in the package is then used to perform quality assurance and finalise the segmentation on each baseline image. Thereafter, TKV will be measured in all follow-up T2-weighted MRI scans using an automated registration-based segmentation technique, as validated previously.^41^ A final quality control check will also be performed on these follow-up scans using the interactive toolkit. Finally, fractional cyst volume will be calculated using an automated cyst segmentation technique along with a final quality check.*Serum and urine electrolytes, creatinine and osmolality*. Outpatient serum and 24 hours urine will be collected at baseline and at months 3, 6, 9, 12, 18, 24, 30 and 36 for measuring electrolytes, creatinine, urea, urate and osmolality. In participants from the intervention group, additional samples will be collected at weeks 3 and 6 for an initial safety check (for hyponatraemia) and for titration of the water prescription. Following the last treatment visit (month 36), blood tests will be performed 2 and 4 weeks later and a 24-hour urine collection will be performed 4 weeks later, in all groups.*Systemic AVP activity*. Venous blood will be collected at all study visits to measure serum copeptin (a pre-pro hormone that is a stable biomarker for AVP). Longitudinal studies show that serum copeptin is a determinant of TKV and eGFR decline in ADPKD^42 43^ consistent with the hypothesis that AVP mediates renal cyst growth. Serum samples will be frozen at −80°C, and copeptin will be measured in batches using a sandwich immunoluminometric assay (CT-proAVP Kryptor, B.R.A.H.M.S, Thermo Fisher Scientific, Germany).
